### Statistical Analysis

Descriptive statistical analysis will be conducted using Microsoft Excel (version 16.16.19; Microsoft Corp) and RStudio (version 1.1463).

For the definitive trial, the following tests will be used to discern relationships between variables: two-sample Welch *t* test for normally distributed continuous variables, Kruskal-Wallis rank-sum test for data without normal distribution, and chi-square goodness of fit test for categorical variables. A *P* value of <.05 will be considered statistically significant.

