## Abstract

**Background:**

Surgical site infections (SSIs) are the most common nosocomial infection and occur in 16.3% of patients undergoing colorectal surgery at our institution (The Ottawa Hospital), the majority of which are identified after discharge from hospital. Patients who suspect having an SSI generally present to the emergency department or surgery clinic. Both options for in-person interaction are costly to the health care system and patients. A mobile app, how2trak, has proven to be beneficial for patients with complex wounds at our institution by facilitating at-home monitoring and virtual consultations.

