## Introduction

### Background and Rationale

Surgical site infections (SSIs) are the most common nosocomial infection among surgical patients, occurring in 5.5% of surgical cases at our institution, The Ottawa Hospital [1]. Similar rates are seen at other centers across North America and Europe, with SSIs impacting 3%-5% of inpatient surgical cases and accounting for 20%-38% of nosocomial infections among surgical patients [2-5]. Patients undergoing colorectal surgery are disproportionately affected. A recent study at our institution found that 24% of patients undergoing colorectal surgery developed an SSI [6]. SSIs are associated with significant morbidity and mortality both in the short and long term. In the initial postoperative period, SSIs are associated with increased postoperative mortality, length of stay, and intensive care unit admission. In the long term, SSIs are independently associated with higher readmission and mortality rates compared to those without an SSI [1].

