### Trial Design

This is an unblinded feasibility randomized controlled trial. Eligible patients will be randomized 1:1 to receive virtual monitoring of their surgical incision, symptoms, and ostomy using H2T or to standard of care.

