#### Definitive Trial Outcomes

The primary outcomes for a definitive trial collected in this study will compare the SSI incidence and severity of patients in the two study arms, as well as their experiences. An SSI is an infection that occurs after surgery in the part of the body where the surgery was performed. A superficial incisional SSI is an infection that involves only skin or subcutaneous tissue of the surgical incision and will be defined using the Centers for Disease Control and Prevention criteria [5].

Secondary outcomes for a definitive trial include hours of in-person interactions with the health care system (including readmissions to hospital, ED visits, and clinic visits), confirmed COVID-19 infection within 30 days after surgery, incidence of postoperative adverse events, and incidence and characterization of ostomy complications.

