### Sample Size

There is no sample size for this feasibility study. It will be conducted over 6 months and we anticipate having 80 eligible patients over this time period.

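### For the planned definitive trial, the article names a chi-square goodness-of-fit test for categorical outcomes, a one-sample test that does not fit the two-arm comparison of SSI incidence

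*Protocol article*

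**What the plan says.** The Statistical Analysis section of the protocol article makes the present study's own analysis descriptive. It then looks ahead: "For the definitive trial, the following tests will be used to discern relationships between variables". The list that follows is a two-sample Welch t test for normally distributed continuous data, a Kruskal-Wallis test for non-normal data, and a "chi-square goodness of fit test for categorical variables". A P "value of <.05 will be considered statistically significant". No other test for categorical data is named, and no reference rate or expected distribution is given.

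Under Definitive Trial Outcomes, the primary outcomes "will compare the SSI incidence and severity of patients in the two study arms", together with patient experience. The secondary outcomes include confirmed COVID-19 infection, postoperative adverse events and ostomy complications, which are at least partly incidence outcomes. Under Trial Design, "Eligible patients will be randomized 1:1".

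Two sections link the present data to that later trial. Informed Consent has patients told that their data may be used in a full-scale trial, with this study as its vanguard. Data Collection and Management plans to incorporate these results if a definitive trial is done.

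**The concern.** A goodness-of-fit test asks whether one observed distribution departs from known proportions. Comparing SSI yes/no between two arms is a different problem, because both proportions are estimated and both carry sampling error. The test for that is the chi-square test of independence (homogeneity), or Fisher's exact test when cells are sparse. The sentence also conflicts with its own stated purpose, since a goodness-of-fit test does not examine a relationship between two variables.

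An analyst who followed the text literally would have to supply the missing expected counts. Different choices give tests with different error rates, so the prespecified P value for a primary outcome of the definitive trial would not be determined by the plan.

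**Working it through.** The article gives no sample size, power or event count for the definitive trial, so there is no figure of its own to reproduce. The benchmark is its 5% level.

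**Inputs**
- Level 0.05 (Statistical Analysis). The chi-square critical value on 1 degree of freedom is 3.841 = 1.96².
- Equal arms of n patients (Trial Design).
- Two SSI risks. The abstract says that SSIs "occur in 16.3% of patients undergoing colorectal surgery at our institution". The Introduction reports that "24% of patients undergoing colorectal surgery developed an SSI".
- n = 40 per arm. This is an assumption for illustration, half of the figure under Sample Size, where "we anticipate having 80 eligible patients over this time period". Values of 100 to 1000 per arm are also assumptions, used to see whether size matters.

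Let T and C be the SSI counts in the intervention and control arms, with the same true risk p in both.

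**Reading A: control counts taken as the expected counts**

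Statistic = (T−C)²/C + (T−C)²/(n−C) = n(T−C)² / [C(n−C)].

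Under the null, Var(T−C) = 2np(1−p), while C(n−C)/n is close to np(1−p). The control arm's variance is left out, so the statistic behaves as 2 × chi-square(1).

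Type I error = P(chi-square(1) > 3.841/2) = 2 × [1 − Φ(1.96/√2)] = 0.166, which is 0.166/0.05 = 3.3 times the stated level.

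If severity were analysed as a categorical outcome with 3 or 4 levels (an assumption; the article gives no number), the same argument gives P(chi-square(2) > 5.991/2) = 0.224 and P(chi-square(3) > 7.815/2) = 0.272.

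**Reading B: SSI events in the two arms tested against a 50:50 split**

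Statistic = (T−C)²/(T+C). The denominator is close to 2np, against a true variance of 2np(1−p), so the statistic behaves as (1−p) × chi-square(1).
- p = 0.163: P(chi-square(1) > 3.841/0.837 = 4.589) = 0.032
- p = 0.24: P(chi-square(1) > 3.841/0.76 = 5.054) = 0.025

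**Test of independence (uncorrected Pearson 2×2)**

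Statistic = (T/n − C/n)² / [p̂(1−p̂)(2/n)], with p̂ = (T+C)/(2n). The asymptotic type I error is 0.050.

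**Exact check**, by enumerating two independent binomials under the null:

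| n per arm (assumed) | p | Reading A | Reading B | Independence |
|---|---|---|---|---|
| 40 | 0.163 | 0.178 | 0.029 | 0.053 |
| 40 | 0.24 | 0.181 | 0.026 | 0.050 |
| 100 | 0.163 | 0.175 | 0.033 | 0.051 |
| 100 | 0.24 | 0.174 | 0.025 | 0.050 |
| 1000 | 0.163 | 0.166 | 0.032 | 0.050 |
| 1000 | 0.24 | 0.166 | 0.025 | 0.050 |

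Under Reading A the statistic is undefined when the control arm has no events; those cases were counted as non-rejections. The departures under A and B do not disappear as the trial grows.

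**The case against.** The strongest reply is that this is a naming slip. The stated aim of relating variables describes a test of independence, the two companion tests both compare groups, and a true goodness-of-fit test could not be run without the reference distribution that the article omits. If a test of independence is what gets run, the type I error is about 5% and only the label is wrong. This is plausible, and it limits the likely harm. It does not correct the text: a test chosen by name should be executable as named, and this is a wrong entry, not a detail left to an analysis plan.

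The second reply concerns reach. The tests are for a definitive trial that will happen only if feasibility is shown. None of the endpoints under Primary Outcome: Feasibility uses a chi-square test, and the wording can be corrected before any between-arm P value is calculated. This stands in full.

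Three stronger inferences are tempting, and the documents do not support them:
- A reader might infer that the SSI comparison will have an invalid P value or a tripled error rate. That holds only under Reading A, and nothing in the article says that the control arm supplies the expected counts.
- A reader might infer that no version of the test respects the 5% level. Reading B rejects less often than 5% under the null, so it does not exceed the level; what it costs is power.
- A reader might infer that the present study's conclusions are compromised. Its analysis is descriptive.

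**Conclusion.** The point holds as an error of specification for the conditional definitive trial: the only categorical test named is a one-sample test, while the planned comparison has two samples. The size of the consequence is hypothetical. It runs from none (a slip, with the independence test actually run), through a conservative 2.5% to 3.2%, to an inflated 16.6% to about 18%, according to how the missing expected counts are filled in. The figures assume equal arms, a common SSI risk of 16.3% or 24%, and arm sizes that the article does not give. The correction is worth making now because the present data may be incorporated into that trial, but it does not stand in the way of the feasibility study.

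**What to change.** In the Statistical Analysis section, replace the goodness-of-fit wording with: chi-square test of independence (Fisher's exact test when expected cell counts are small). Reporting a risk difference with its 95% confidence interval alongside the P value is optional. The change should be in place before any between-arm P value is calculated. It costs one sentence of analysis text and does not touch data collection, randomisation or the feasibility endpoints.

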### Sample Size

There is no sample size for this feasibility study. It will be conducted over 6 months and we anticipate having 80 eligible patients over this time period.

### Assignment of Interventions

After written informed consent is obtained, eligible patients will be randomly assigned to either the intervention or control group using a secure web-based randomization system at the Methods Centre of The Ottawa Hospital Research Institute. This study will be unblinded so no attempts at concealment of patients’ allocation will be made.

### Data Collection and Management

Data will be captured through the assessments and/or photographs in H2T and the hospital’s electronic health information system (Epic). Data sent from H2T to The Ottawa Hospital—including patient identifiers to allow for merging with Epic data—will be transferred through a secure, access-controlled folder within Office 365. Once the data files are merged, they will be deidentified. Only research personnel will have access to the study data. A data monitoring committee will not be developed given the minimal risk and small sample size of this feasibility trial.

If a definitive trial is completed, we plan to incorporate the results of this study into the data collection of the trial.

### Confidentiality

Data will be originally stored locally on patients’ devices, encrypted, in a secure app sandbox of the H2T app. The H2T app will attempt to synchronize its internal database with the server's database whenever there is a need (ie, new information is created). Once the data are on the server, they will be retained with patient identifying information intact for a length of time (such as 6 or 10 years), as determined by the requirements of the jurisdiction in which the data is being collected.

The Ottawa Hospital data will be collected primarily from Epic using Workbench reports. Data from Health Outcomes Worldwide’s encrypted servers will be securely transferred to the research team, who will merge it with data collected primarily from Epic using patients’ names and partial dates of birth as identifiers (entered by patients when developing their login). A master list (containing the study ID and patient identifiers) will be accessible only to the researchers responsible for the analysis and will be kept separate from the main study data set in a secure, access-controlled folder on The Ottawa Hospital’s Office 365 cloud. The Ottawa Health Science Network Research Ethics Board (OHSN-REB) and Ottawa Hospital Research Institute may review relevant study records (under the supervision of the investigator) for audit purposes.

### Oversight and Monitoring: Adverse Event Reporting and Harms

Clinicians involved in the trial (surgical team and virtual care NSWOC) will monitor for adverse events and report them immediately to the Principal Investigator. The investigator team will report to the Research Ethics Board any adverse event that is deemed to be unexpected, related or possibly related to the investigational product or other study intervention/treatment/procedure or to participation in the research (ie, definitely, probably, possibly, or unlikely related) and that involves greater risk.

If the adverse event meets reporting criteria, the event will be submitted within seven calendar days of the team becoming aware of the incident using the OHSN-REB Reportable Events form. There are no plans for audits of the trial conduct.

## Results

This study was approved by the OHSN-REB on February 26, 2021, and accepted for The Ottawa Hospital Innovation and Care Funding on November 12, 2021. Recruitment started June 3, 2021, and as of September 2021, we had 29 patients enrolled. We expect to publish results in spring 2022.

## Discussion

We anticipate this work will help us to better understand the feasibility of using mobile technology to optimize patients’ care after discharge from hospital after colorectal surgery. Virtual postsurgery wound and symptom monitoring could enhance the patient experience, SSI detection, and reduce the risk of COVID-19 transmission. If this technology is feasible for our patient population and workflow, we plan to formally assess its effectiveness with a definitive trial. The H2T app has multiple functionalities, and this study could establish a framework for assessing its use in other domains including ostomy monitoring and patient education, as well as for patients undergoing other surgical procedures.

## Appendix

Multimedia Appendix 1 Supplemental materials.

## Abbreviations

CONSORT-EHEALTH: Consolidated Standards of Reporting Trials of Electronic and Mobile Health Applications and Online Telehealth
ED: emergency department
H2T: how2trak
NSWOC: Nurse Specialized in Wound, Ostomy, and Continence
OHSN-REB: Ottawa Health Science Network Research Ethics Board
PSSUQ: Post-Study System Usability Questionnaire
SPIRIT: Standardized Protocol Items: Recommendations for Interventional Trials
